## 4. PARTICIPANT ENROLLMENT AND WITHDRAWAL

### 4.1 Recruitment

Following receipt and signing the MAIN study consent forms, subjects will be fully informed of the nature of this optional EXPLORATORY STUDY, and the specific risks associated with this EXPLORATORY STUDY. A separate 'Participation Information Sheet and Consent Form' will be provided for this purpose (Appendix D).

The 'Informed Consent' will be signed and dated by the participants in the presence of an investigator. Subjects will also be given a copy of their signed 'Informed Consent'. A copy of the HIRF site map (Appendix E), diet and activity sheet (Appendix C) and F FDG Product Information (FDA information, see section 12. Appendix G) will be provided for participant reference.

### 4.2 Eligibility Criteria

#### 4.2.1 Inclusion Criteria

In order to be eligible to participate in this study, an individual must meet all of the following criteria:

- Provide signed and dated informed consent form
- Able to lie supine and still for duration of image acquisition
- All other criteria as outlined in MAIN study protocol(s)

#### **4.2.2 Exclusion Criteria**

An individual who meets any of the following criteria will be excluded from participation in the study:

- Known allergic reactions to components of the study radiotracer  $^{18}\text{F}$  FDG
- Fasted screening blood glucose elevated above the normal range (BSL >6.0mmol/L)
- Failure to meet/provide the standard MRI checklist requirements
- Claustrophobia precluding image acquisition
- Significant previous radiation exposure as defined (lifetime exposure):
  - Any fluoroscopic imaging (e.g. coronary angiography)
  - Any nuclear medicine imaging (e.g. myocardial perfusion scan)
  - Greater than one previous CT scan
  - *Note:* previous plain film X-Rays and mammography are acceptable
- All other criteria as outlined in MAIN study

#### **4.3 Participant Withdrawal**

Participants have the right to withdraw from the study at any time for any reason. The investigator also has the right to withdraw patients from the study in the event of any clinical adverse event (AE), laboratory abnormality, or other medical condition or situation occurs such that continued participation in the study would not be in the best interests of the participant OR the participant meets an exclusion criterion (either newly developed or not previously recognized) that precludes further study participation.

Following consent, data acquired up until withdrawal will be included in the EXPLORATORY STUDY. No further samples will be collected from the time of withdrawal notification.

#### **4.4 Permanent Termination or Suspension of Exploratory Study**

The principal investigator(s), Human Research Ethics Committee (HREC) and Regulatory Authorities independently reserve the right to discontinue the study at any time for safety or other reasons. This will be done in consultation with the MAIN study sponsor where practical. The MAIN study sponsor, in consultation with the investigators may request for suspension of the EXPLORATORY STUDY.

After such a decision, the investigator(s) will ensure that adequate consideration is given to the protection of the participants' interests. The investigator must review all participants as soon as practical and complete all required records.

### **5. STUDY INVESTIGATIONS**

Whole body imaging will be performed using the Biograph mMR PET/MRI system, with concurrent PET and MRI acquisition. Dedicated Brain MRI sequences will be performed using the MAGNETOM Prisma 3T MRI system. This equipment is property of HIRF.

The standard radiotracer  $^{18}\text{F}$  FDG will be used for PET imaging. This radiotracer has previously been approved by the Australian Register of Therapeutic Goods as a consumable for use in PET imaging (Austin Health) and attracts an MBS rebate for use in multiple conditions.)

The radiotracer is to be purchased from the RBWH Nuclear Medicine Department, a TGA licensed manufacturer of  $^{18}\text{F}$  FDG. The  $^{18}\text{F}$  FDG is produced under the Good Manufacturing Practice (GMP) conditions (see Appendix F) in accordance with the British Pharmacopeia. The research will not alter the formulation of the product. The research will be using an identical product in an identical way in an identical formulation to that used for clinical diagnostic PET imaging.  $^{18}\text{F}$  FDG is supplied as a clear/colourless or slightly yellow solution containing the radionuclide  $^{18}\text{F}$  conjugated to the biologically active ligand glucose. It is administered as an intravenous injection prior to imaging.

All radiotracer for use will be released as per existing RBWH Nuclear Medicine department practices. Dosing of the radiotracer is at a standard weight-based dosage. This is determined based on participant radiation exposure, not pharmacological effect. The effective dose of the metabolically active ligand (FDG) is considered a micro-dose.

Due to the unique nature of radiopharmaceuticals  $^{18}\text{F}$  FDG is considered an investigational product by the TGA for purposes of this research project.

### **5.1 Radiotracer Dosing Regimen**

- Prior to administration of  $^{18}\text{F}$  FDG participants are to fast for roughly 6 hours.
- Prior to administration of  $^{18}\text{F}$  FDG participants are to avoid strenuous exercise and adhere to a low carbohydrate diet for 24 hours.

An estimated dose of 4.5MBq per kg (based on screening weight)  $^{18}\text{F}$  FDG is to be administered by infusion (minimum dose 90MBq, maximum dose 400MBq). This is the lowest possible dose to yield reliable data. The radioactive half-life of  $^{18}\text{F}$  FDG is 110 minutes. Estimated radiation exposure is included in the radiation assessment report (see Appendix A).

- Following administration of  $^{18}\text{F}$  FDG participants are encouraged to drink water to promote the renal excretion of radiotracer.

### **5.2 Modification of Radiotracer Administration for a Participant**

Any participant experiencing an AE to any part of the investigation (participation in imaging process or infusion of radiotracer) will be individually evaluated. Where it is considered unsafe to repeat the process by the investigator(s) in discussion with the Nuclear Medicine Independent Medical Advisor, no further imaging will take place.

### **5.3 Participant Compliance**

Participant non-compliance with preparation for image acquisition or non-compliant with instruction during imaging itself (e.g. excessive movement) will be recorded in

the participant file as this may have an impact on the quality of data collected. This will include reference to the diet and exercise activity sheet assessed prior to imaging.

#### **5.4 Radiotracer Manufacture, Handling and Accountability**

The formulation, packaging and labeling of the standard radiotracer  $^{18}\text{F}$  FDG is defined by licensed manufacturer. The  $^{18}\text{F}$  FDG is stored at room temperature in accordance to the conditions set by the manufacturer. Handling of the radiopharmaceutical will follow the standard HIRF protocols for all injectable radiopharmaceuticals

The  $^{18}\text{F}$  FDG will be ordered on an as needed basis. The  $^{18}\text{F}$  FDG is supplied on the day of each study. The product expiry time is on the same day as supply due to the short half life of the radioactive element. There will be no excess product. The administration of the GMP approved standard radiotracer  $^{18}\text{F}$  FDG will be as per existing HIRF practices, including record keeping of  $^{18}\text{F}$  FDG lot number, patient injected activity and time of administration using the Venstra system. Product accountability and quality control will be as per existing RBWH Nuclear Medicine Department practices under the Quality GMP Agreement for TGA licensing for the manufacture and supply of radiopharmaceuticals.

### **6. STUDY SCHEDULE**

#### **6.1 Screening**

Participants consenting for participation in this EXPLORATORY STUDY must meet all inclusion and exclusion criteria for both MAIN and EXPLORATORY STUDY participation.

This includes EXPLORATORY STUDY specific screening for:

- Fasted blood glucose (exclude if  $>6.0\text{mmol/L}$ )
- Significant prior radiation exposure precluding participation (see exclusion criteria)
- MRI checklist completion, including evaluation for claustrophobia and ability to comfortably lie supine that may preclude participation
- Evaluation of patient understanding of preparation for imaging acquisition instructions: fast 6 hours prior; abstain from vigorous exercise and adherence to low carbohydrate diet 24 hours prior.

#### **6.2 Enrollment/Baseline**

Baseline fasted blood glucose and MRI checklist must be completed. Low carbohydrate diet options will be discussed.

#### **6.3 Intermediate Visits**

The first visit (within one week prior to MAIN study inoculation) will include advanced medical imaging.

#### **6.4 Final Exploratory Study Visit**

The second visit (MAIN study one to two days prior to confinement) will include advanced medical imaging. This will also be the final study visit. Any AEs that require follow up will be reviewed at subsequent MAIN study visits.

## **6.5 Withdrawal Visit**

A withdrawal visit coinciding with a scheduled MAIN study visit (or MAIN study withdrawal visit) will take place to review imaging results as required.

## **6.6 Unscheduled Visit**

There are no unscheduled visits expected for this EXPLORATORY STUDY. In any case where an unscheduled visit is required, attempts will be made to ensure this occurs at a pre-existing MAIN study visit.

# **7. STUDY PROCEDURES AND EVALUATIONS**

## **7.1 Study Procedures**

Medical history, medication history, physical examination and biological specimen collection as per MAIN study.

EXPLORATORY STUDY specific procedures include:

Screening visit:

- Completion of MRI checklist at screening visit – consultation between participant and study doctor
- Recording of radiation exposure history at screening visit – consultation between participant and study doctor
  - radiology including plain films, CT scans, mammography, fluoroscopy and nuclear medicine (both diagnostic and interventional).
- Participant education regarding preparation for PET/MRI imaging
  - Low carbohydrate diet advice and information sheet
  - Discussion of physical activity limitation in pre-imaging period

Attendance for imaging:

- Insertion of peripheral intravenous cannula (as per MAIN study) for blood collection and radiotracer administration
- Capillary blood glucose measurement if clinical concerns
- Urine pregnancy testing for female participants of child bearing potential if not performed as part of MAIN study protocol within 24 hours prior.
- Whole body PET/MRI imaging
  - abstinence from physical activity for >24 hours prior recorded (or type of activity recorded for consideration during interpretation if participant noncompliant with instruction)
  - low carbohydrate diet for >24 hours prior and fasting for roughly 6 hours prior recorded
  - insertion of a peripheral intravenous cannula
  - review of MRI checklist
  - infusion of  $^{18}\text{F}$  FDG via peripheral intravenous cannula
  - image acquisition – participant supine on scanner for duration of image collection
  - image review and reporting by specialist radiologist
  - $^{18}\text{F}$  FDG uptake quantification by Patlak model analysis by medical physicist, SUV semi-quantification of remaining regions of interest
- Dedicated MRI imaging
  - image acquisition – participant supine on scanner for duration of image collection

- image review and reporting by specialist radiologist

## **7.2 Laboratory Procedures/Evaluations**

### **CLINICAL LABORATORY EVALUATIONS**

MAIN study fasted blood glucose measurements will be used as part of the EXPLORATORY STUDY screening process.

Bedside capillary blood glucose measurement will take place prior to PET/MRI scanning if there are clinical concerns.

Urine point of care pregnancy testing will be performed at either of QPharm or HIRF within 24 hours prior to PET/MRI imaging.

MAIN study baseline and serial safety blood tests (full blood count and biochemistry) will be used for comparison of imaging results.

### **SPECIAL ASSAYS OR PROCEDURES**

Collection of blood samples for parasitaemia and parasite biomass measurements will take place as part of the MAIN study protocols.

## **8. ASSESSMENT OF SAFETY**

### **8.1 Specification of Safety Parameters**

As per MAIN study

### **8.2 Definition of an Adverse Event and of a Serious Adverse Event**

#### **ADVERSE EVENT**

Any untoward medical occurrence in a patient or clinical investigation participant administered a pharmaceutical product and which does not necessarily have a causal relationship with this treatment. An AE can therefore be any unfavorable and unintended sign (including an abnormal laboratory finding), symptom, or disease temporally associated with the use of a product, whether or not related to the product.

#### **SERIOUS ADVERSE EVENT**

A serious AE is any untoward medical occurrence that, at any dose:

- a) Results in death
- b) Is life threatening (the term 'life-threatening' in the definition of 'serious' refers to an event in which the participant was at risk of death at the time of the event. It does not refer to an event, which hypothetically might have caused death if it were more severe.
- c) Required hospitalization or prolongation of an existing hospitalization (hospitalization for elective treatment of a pre-existing condition that did not worsen from baseline is not considered an AE)
- d) Results in disability/incapacity
- e) Is a congenital abnormality/birth defect.

Use medical and scientific judgment when deciding whether reporting is appropriate in other situations, such as other important medical events that may not be immediately life-threatening or result in death or hospitalization, but may jeopardize the participant or may require medical or surgical intervention to prevent one of the outcomes listed in the above definition.

#### **SUSPECTED UNEXPECTED SERIOUS ADVERSE REACTION (SUSAR)**

A suspected unexpected serious adverse reaction is an AE that is determined to be related to the radiotracer and is both serious and unexpected. The term 'unexpected' means that nature or severity of the event is not consistent with the applicable product information (Appendix G.)

### **8.3 Documentation and classification of study specific adverse events**

For regulatory purposes to use the standard radiotracer  $^{18}\text{F}$  FDG in this EXPLORATORY STUDY all AEs deemed related to radiotracer administration will be documented in an EXPLORATORY STUDY AE log including diagnosis, severity, toxicity, date of onset and resolution and any action taken. Toxicity will be determined using existing CTCAE version 4.0 criteria, consistent with those proposed for use in the MAIN studies. Severity will be determined based on the following scale:

- Mild: does not interfere with participant's usual function
- Moderate: interferes to some extent with participant's usual function
- Severe: interferes significantly with participant's usual function

All AEs will be recorded in the MAIN study participant file as per MAIN study processes. Where an AE is deemed a result of EXPLORATORY STUDY activities ( $^{18}\text{F}$  FDG radiotracer administration or other imaging procedures), this will be made clear in documentation and discussed with the MAIN study principal investigator prior to any appropriate escalation to MAIN study medical monitor and sponsor.

### **8.4 Relationship to Study Investigation**

For the purposes of this study for an AE to be considered related to  $^{18}\text{F}$  FDG it must occur within 5 half-lives, or 550 minutes of administration. For an AE to be considered related to other imaging procedures, it must occur during the procedure itself.

Any AEs deemed related to the above EXPLORATORY STUDY procedures will be documented in the EXPLORATORY STUDY AE log by one the Investigator or one of his representatives.

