### **8.5 Recording and Prompt Reporting of Events**

In all cases of AEs, the reporting process used for the MAIN study from which the participant was recruited will be used. If MAIN study procedures are not available recording and reporting of AEs will be in accordance with QIMRCTSOP013 and QIMRCTSOP016.

Any AE deemed related to the administration of  $^{18}\text{F}$  FDG or other imaging procedures will be discussed where possible to further clarify causality with the nominated Nuclear Medicine Independent Medical Advisor.

Any SAE deemed related to the administration of  $^{18}\text{F}$  FDG or other imaging procedures will be reported to the Sponsor within 24 hours following discussion with the medical monitor and where possible with the nominated Nuclear Medicine Independent Medical Advisor. The TGA and any other relevant authorities will be notified by the Sponsor (or institutionally approved representative) within 72 hours as per existing TGA guidelines.

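### Section 8.4 makes onset time a required condition for calling an adverse event related to imaging, so a later event the investigator attributes to the tracer or cannula must be classed as unrelated

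*Supplement*

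**What the plan says.** Section 8.4 (Relationship to Study Investigation) gives two timing rules. For the tracer, "for an AE to be considered related to" FDG "it must occur within 5 half-lives, or 550 minutes of administration". For the rest of the visit, "For an AE to be considered related to other imaging procedures, it must occur during the procedure itself". Section 5.1 supplies the half-life: the radioactive half-life of "FDG is 110 minutes".

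The call of relatedness then controls what follows. Section 8.4 continues: "Any AEs deemed related to the above EXPLORATORY STUDY procedures will be documented in the EXPLORATORY STUDY AE log". Section 8.3 states the entry rule for tracer events: "all AEs deemed related to radiotracer administration will be documented in an EXPLORATORY STUDY AE log". Under section 8.5, an AE already deemed related to FDG or another imaging procedure "will be discussed where possible to further clarify causality with the nominated Nuclear Medicine Independent Medical Advisor", and an SAE deemed related goes to the sponsor within 24 hours. The SUSAR definition in section 8.2 also requires relatedness to the radiotracer.

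Three other places matter. Section 7.1 lists peripheral cannula insertion as a step of the PET/MRI attendance. Section 8.3 sends every AE to the MAIN study participant file. Section 12 (Regulatory Authorities) gives the independent nuclear medicine advisor the continuing review of SAEs that might be linked to the study's activities, which is a wider test than in 8.5.

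**The concern.** A time window is useful evidence on causality. Here it is worded as a condition that has to be met, and nothing allows an investigator to judge otherwise. The protocol offers no evidence that reactions start within 550 minutes. The figure comes from radioactive decay, whereas the two FDG reactions described in section 8.4 under expectedness are a probable skin reaction and a possible anaphylaxis. The procedure rule is stricter, because it allows no time at all after the procedure ends.

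What is at stake is the completeness of the safety record that this study keeps for the regulator. Section 12 says the CTN registration is there so that tracer use is recorded prospectively and openly, including AE reporting. A rule that settles causality by the clock, ahead of the step meant to clarify causality, works against that purpose.

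**Working it through.** **1. The plan's figure.** Half-life 110 min (section 5.1); number of half-lives 5 (section 8.4). 5 × 110 = 550 min = 9 h 10 min, so the stated figure reproduces exactly. Activity left after five half-lives is 0.5^5 = 3.1%. That is what the window describes; it says nothing about when a reaction begins.

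**2. The procedure window.** Time allowed after the end of the procedure: zero. Even if the whole HIRF visit of about 4 hours (section 3) is counted as the procedure, a cannula-site event that starts after departure cannot be called procedure-related. A site event starting within 550 minutes could be logged only if it were attributed to tracer administration instead of to the cannula.

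**3. A late event followed through the text.** Suppose an event starts after the limit and the investigator believes the tracer or the cannula caused it.

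| Step | Entry condition | Late event |
|---|---|---|
| MAIN study file (8.3) and MAIN reporting process (8.5) | Any AE | Recorded, but not as related to imaging |
| Exploratory AE log (8.3, 8.4) | Deemed related | Excluded |
| Advisor's AE causality discussion (8.5) | Deemed related | Excluded |
| 24-hour sponsor report (8.5) | SAE deemed related | Excluded |
| SUSAR (8.2) | Determined related to the tracer | Excluded |
| Advisor's SAE review (12) | Possible link | Included on its own wording, at odds with 8.4 and 8.5 |

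Sections 8.3 and 8.4 also differ on scope: the log sentence in 8.3 names tracer events only, while 8.4 includes imaging procedures.

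**4. Exposure.** Section 3 allows up to eight participants with two scans each: 8 × 2 = 16 administrations. The linked protocol adds 2 × 2 = 4.

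**5. Expected count.** Section 8.4 of the eight-participant protocol cites 2.1 AEs per 100 000 radiopharmaceutical administrations. 16 × 2.1 / 100 000 = 0.0003 tracer events, whatever their onset. The documents give no rate for cannula-site events.

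**6. Share that would fall outside (assumption only).** The documents give no onset times. If onset were exponential with median m hours, the share falling after a window of w hours would be 0.5^(w/m).

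| Assumed median onset | After 9 h 10 min (tracer) | After a 4 h visit (procedure) |
|---|---|---|
| 6 h | 35% | 63% |
| 12 h | 59% | 79% |
| 24 h | 77% | 89% |
| 48 h | 88% | 94% |

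The share depends heavily on an onset time that the plan does not provide. The table shows only this and estimates nothing for this study.

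**The case against.** The best defence is that late events have somewhere to go. Every AE is entered in the MAIN study file, the MAIN reporting process applies to all of them, and follow-up continues at MAIN visits (sections 8.3, 8.5 and 6.4). Section 5.2 has any participant with an AE from the investigation evaluated individually, with the advisor consulted on whether imaging may be repeated, and it sets no time limit. Section 12 gives the advisor SAEs with a possible link. Cannulation is done as in the MAIN study, so MAIN AE handling covers it. Very few tracer events are expected. All of this stands, and it limits the point to attribution and routing.

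Stronger readings are tempting, but the documents do not support them:

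- **That the log must report no related events.** Events judged related that start inside the window, or during a procedure, are logged.
- **That late events escape the advisor altogether.** Sections 5.2 and 12 say otherwise for repeat-imaging decisions and for SAEs.
- **That late events will be blamed on the inoculum or the MAIN study drug.** This depends on MAIN causality rules that are not shown, and the first scan precedes inoculation.
- **That tracer or cannula reactions typically start late.** No onset time is given, including for the two published cases.

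The defence does not answer the wording of 8.4. The rule still obliges an investigator who suspects imaging to record the event as unrelated, and 8.5 still begins from events already deemed related.

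**Conclusion.** The point holds as a fault in the classification rule. Section 8.4 makes timing necessary for relatedness, on a basis that describes decay, with no window after the procedure for cannulation and no room for judgement. A later event suspected to come from imaging stays in the MAIN study file as unrelated to imaging. It is kept out of the exploratory log, the advisor's AE discussion in 8.5, and the related-SAE and SUSAR route. Sections 8.4 and 8.5 also conflict with the wider review that section 12 assigns to the advisor.

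The exposure is up to 16 administrations in the eight-participant protocol and 4 more in the linked one. The effect on event counts is probably very small and cannot be estimated from the documents. The conclusion assumes that 8.4 is applied as written; it does not depend on any assumed onset time. The wording should be corrected, but the fault does not threaten the imaging results.

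**What to change.** 1. In section 8.4, replace the mandatory wording in both timing sentences with a statement that onset in the given period supports a causal link but is not required for one.
2. Enter in the exploratory log any AE that the investigator judges possibly related to the tracer, cannulation or imaging, whatever its onset time. State the same scope in 8.3 and 8.4.
3. Align 8.3 and 8.5 with section 12, so that AEs with a possible link go to the independent advisor for an opinion on causality.
4. Make the same change in the linked two-participant protocol.

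The cost is a few sentences and possibly a few extra log entries, some of which may turn out to be malaria symptoms after the second scan. Logging every AE up to the next MAIN visit is not needed and would bring more such symptoms into the log. No participant procedure changes.
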